### Paper and study aims

This paper aims to describe how *Dove Confident Me Indonesia: Single Session* was culturally adapted for use in Indonesian junior high state schools. It details the methods that will be employed to evaluate the intervention’s effectiveness and acceptability in a randomised controlled trial, as well as considerations for conducting this research during the COVID-19 pandemic. It also provides the plan for dissemination and highlights the strengths and limitations of the research trial study design.

The aim of the study outlined in this paper is to evaluate *Dove Confident Me Indonesia: Single Session*, as delivered online to students by schoolteachers or school guidance counsellors working in Indonesian state schools, in terms of intervention effectiveness and acceptability. Although originally designed to be delivered in a face-to-face format in school classrooms, project partners made a collaborative decision to evaluate the effectiveness of the intervention delivered in an online setting (i.e., via virtual video-conferencing classrooms) in response to the ongoing COVID-19 pandemic.^2^ Considering this adaptation, this study aims to assess the acceptability of the curriculum and pedagogy with students and teachers as well as the programme’s effectiveness in improving body esteem and related psychosocial outcomes. In line with previous evaluations of single-session body image interventions [36], we anticipate the intervention to provide short-term (up to two months follow-up) improvements in body image compared to a wait-list control group in order to assess the absolute impact of the intervention. Moreover, in line with the Tripartite Influence Model [51] and the targeted risk factors *Dove Confident Me Indonesia: Single-Session* aims to address, we anticipate a short-term reduction in internalisation of appearance ideals and appearance comparisons, alongside a reduction in the extent to which negative body image prevents adolescents from engaging in life activities relative to the wait-list control group. Finally, due to cultural adaptations of the original programme to challenge harmful skin shade ideals in Indonesia, we anticipate short-term improvements in skin shade satisfaction.

## Method

### Intervention design

To develop *Dove Confident Me Indonesia: Single Session* for use across Indonesian schools, it was necessary to culturally adapt the programme content, as well as modify the pedagogical format to accommodate modest school resources (e.g., no PowerPoint projector and limited internet access) so that the intervention is accessible to all schools across Indonesia, regardless of available resources. The main cultural adaptations are evident in the imagery and cultural examples used throughout the programme materials (i.e., photos and illustrations of Indonesians), role-play scenarios (e.g., aspirations to be a YouTuber), and discussions regarding cultural influences, such as K-pop. To accommodate limited resources, all video and PowerPoint content was removed, and more information, context, and imagery were added to the student worksheets.

Consistent with the development of other body image programmes including the original version of *Dove Confident Me: Single Session* [36], as well as general health intervention development best practice [52, 53], the adaption of *Dove Confident Me: Single Session* for an Indonesian context involved a rigorous and iterative community participatory design process. This included a careful review of existing effective body image interventions and the study of relevant theory, preliminary topic-related focus group discussions with Indonesian adolescents and teachers (led by UNICEF Indonesia and Girl Effect^3^ in partnership with Cimigo, a local research agency), as well as continuous consultation and collaboration among various academic, industry, and community stakeholders. Stakeholders in the present project include UNICEF Indonesia, which provides education, youth, health, and gender expertise; Indonesian academics, health professionals, and schoolteachers, who provide cultural context and expertise (authors CR, BEM, KN, and LAS); the Indonesian Ministry of Education and Culture; and Indonesian adolescents. Table 1 provides a summary of the intervention development process.

**Table 1 Tab1:** Intervention Development Process Summary

Activity	By Whom	When
Preliminary focus groups with adolescents and schoolteachers in Sorong, West Papua and Bone, South Sulawesi exploring themes related to body image and appearance pressures and reviewing existing DSEP materials, including *Dove Confident Me*.	UNICEF Indonesia	March 2019
Literature review of theory and existing evidence-based body image interventions.	Authors: NC, KMG, SH	October–December 2019
Focus groups with adolescents and schoolteachers in Sorong, West Papua and Bone, South Sulawesi to test a selection of activities and to further understand the needs of Indonesian adolescents regarding body image as well as the needs of Indonesian teachers in terms of training requirements.	UNICEF Indonesia, Innovesia (research agency)	January–February 2020
Online focus groups with adolescent girls in Greater Jakarta exploring themes related to body image.	Girl Effect (non-profit organisation), Cimigo (research agency)	March 2020
Iterative content and language revisions of the curriculum based on the original evidence-based intervention working with both the English and Bahasa Indonesia versions of the programme.	Authors: NC, KMG, SH, PCD, CR, KN, BEM, and LAS	April–June 2020
Formal government review of curriculum involving ministry officials, education and health experts, and experienced teachers from different regions across the country.	Indonesia Ministry of Education and Culture	June 2020
Final content revisions to the Bahasa Indonesia language version of the curriculum plus final proofing (spelling and grammar).	Authors: NC, KMG, SH, PCD, CR, KN, BEM, LAS, UNICEF Indonesia, and translator (AW)	July 2020
Development of the design version of the curriculum (to include pictures and illustrations).	UNICEF Indonesia plus authors NC, SH, KMG, PCD, and DSEP for the Spot the Difference task	April–December 2020

Aligned with UNICEF Indonesia’s LSE curriculum, *Dove Confident Me Indonesia: Single Session* features skills-based, active learning via class discussions, small group activities, role plays, and individual tasks, all of which have embedded critical thinking and respect for diversity, tenets of the LSE curriculum. All materials (i.e., the teacher guide, teacher e-learning module, and student worksheets) are in Bahasa Indonesia, the national language of Indonesia. See Table 2 for an overview of the intervention content and associated techniques that address the targeted risk factors.

**Table 2 Tab2:** Dove Confident Me Indonesia: Single Session Intervention Summary

Activity	Activity details	Therapeutic technique(s)	Risk factor target(s)
Introduction	1) Define body confidence (high body esteem). 2) Explain why body confidence is important. 3) Share information on the current state of body confidence among Indonesian boys and girls.	Psychoeducation	n/a
Activity One: Appearance Ideals – the ‘Perfect-Looking” Girl/Boy	1) In small same-gender groups, students generate and record physical attributes that comprise the 'ideal' appearance for girls or for boys in their student worksheets (see Fig. 3). 2) Guided class discussion critically exploring societal appearance ideals (i.e., changes over time, differences across cultures, relevant influences, are they realistic?).	Psychoeducation	Internalisation of appearance ideals
Activity Two: Is It Worth It?	1) Guided class discussion examining the costs of pursuing societal appearance ideals related to time, money, emotions, health, and relationships. 2) In small groups, students record the costs using silhouettes provided in their student worksheets (i.e., individual costs are recorded inside the silhouette; community and societal costs are recorded outside the silhouette). 3) As a class and then in pairs, students share why pursuing societal appearance ideals is a bad idea.	Cognitive dissonance	Internalisation of appearance ideals
Activity Three: Spot the Difference	1) In small groups, students analyse the differences in four pairs of photos (provided in their student worksheets) displayed in a 'before' and 'after' format in which the 'after' photo has been digitally altered (see Fig. 4). 2) Small groups discuss the techniques used on social media to change one’s appearance before and after a photo is taken; the impacts on young people; who benefits from digital alteration; and why it is unfair.	Media literacy Cognitive dissonance	Internalisation of appearance ideals Media pressure Comparison
Activity Four: Supporting Others to Be Body Confident	1) In pairs, engage in role plays of specific scenarios (provided in the student worksheets) in which one student must persuade the other to not compare themselves to media images and to not pursue societal appearance ideals. Each student must take on the role of the persuader. (See Fig. 5). 2) Guided class discussion on how media images are unreal and how comparison with them can be harmful.	Cognitive dissonance	Internalisation of appearance ideals Media pressure
Take-Home Challenge: Mirror Exercise	1) While standing in front of a mirror, students make a list of three things they value about their personality, three body parts they like because of what it allows them to do, and three body parts they like how they look. 2) While still in front a mirror, students say, “I like my XX” using the features they generated in their list.	Cognitive reframing (e.g., to think about body functionality) Self-affirmation	Self-esteem Attention bias
Conclusion	1) Each student writes down at least one thing they will do to promote body confidence (examples are provided). 2) Students sign and date these commitments. 3) Provide students an opportunity to share their commitments with the class.	n/a	n/a

In order to facilitate the lesson, all teachers and school guidance counsellors will be required to complete 4.5 h of online training, which consists of an online self-guided e-module (approximately 90 min) and two online synchronous training sessions (90 min each). The e-module training course in Bahasa Indonesia for the entire UNICEF Indonesia LSE programme including the body image lesson was designed by UNICEF Indonesia and Sentra Studia, a local digital agency. The study authors consulted on the design and content of the body image lesson section of this training. This complete training course will be available online by the Indonesian Ministry of Education and Culture for all state schoolteachers to complete prior to delivering the LSE curriculum in exchange for continued education credits. As part of this study, participating teachers and school guidance counsellors will be asked to complete the body image component of the e-module training only. Next, following the e-module training, participating teachers and school guidance counsellors will be required to attend two 90-min online group training sessions on the body image lesson, facilitated by a member of the research team (CR) on a virtual video-conferencing platform in Bahasa Indonesia. In the first session, teachers will learn about body image and will take part in a walk-through of the lesson (as ‘students’), which will be facilitated by CR. In the second session, teachers will practice delivering lesson activities, receive peer and trainer feedback on their teaching practice, and have the opportunity to ask any questions regarding the intervention.

### Internal pragmatic pilot study

Before commencing with the main cluster RCT evaluation, we will conduct a pragmatic internal pilot to assess the feasibility of recruiting and retaining participants to the online trial, as well as assessing preliminary acceptability of the intervention. The pilot will be conducted with two schools, with two classes per school (grades 7 and 8). The schools will be randomly allocated to either the intervention or wait-list control group. We expect approximately 60 students to participate per school, a sufficient sample size for testing the feasibility of a trial [54]. The pilot consent process will be the same as is detailed for the main trial. Two teachers or school guidance counsellors at the intervention condition pilot school will be trained to deliver the lesson by a member of the research team (CR). They will also be asked to complete the body image component of the UNICEF LSE teacher training e-module as previously detailed.

Participating students in the intervention condition school will take part in the *Dove Confident Me Indonesia: Single Session* lesson facilitated by one of the trained teachers with their class peers (up to 30 students per group) via a video-conferencing platform. They will complete the online survey assessment three times in line with the main trial timings: One week prior to the lesson (T1), 1 week after the lesson (T2), and 8 weeks after the lesson (T3). Lesson fidelity will be assessed by trained members of Cimigo, the local research agency conducting the research, following a checklist as well as a member of the research team (KN). Students in the intervention condition will also be asked to provide feedback on the acceptability of the lesson as well as the experience of participating in the lesson (including the use of breakout rooms) at the end of the T2 online survey. Further, two focus group discussions with students took part in the lesson (one group of girls, one group of boys) and two individual interviews with the teachers who delivered the lesson will be held to gather insights on the acceptability of the lesson. Participating students in the wait-list control condition will complete the three online survey assessments in parallel with the intervention condition (T1, T2, and T3). The school allocated to the wait-list control will be provided with lesson materials following T3. Feasibility feedback on the research procedure will be collected from Cimigo.

Progression criteria based on (i) recruitment, (ii) participant retention, (iii) adherence to intervention, and (iv) lesson fidelity will be used to ascertain how we proceed from the pilot to the main trial. In addition, though adverse effects of the intervention or research trial are not expected based on findings from similar previous intervention studies (e.g., [36, 37, 49]), the research team will screen the data for safety (e.g., trends indicating declining body esteem). Criteria will be rated for each parameter with a traffic light system from red (stop, major issue for the progress of the trial) through to amber (amend and proceed with caution) through to green (continue, no issues threatening the success of the trial) [55]. The progression criteria are presented in Table 3.

**Table 3 Tab3:** Progression Criteria from Pragmatic Pilot to Main Trial

Criteria		Green	Amber	Red
Recruitment	How many parents consent and corresponding students assent (target *n* = 120)	**50% or above** Continue with main trial	**30 and 49%** Consult research team to advise on changes to recruitment plan	**Below 30%** The pilot study may need to be extended
Participant Retainment	Student completion up until T2 in both arms	**70% or above** Continue with main trial	**50–69%** Consult research team to advise on changes to survey administration protocol	**Below 50%** The main trial will need to reconsider how surveys are administered
Intervention Adherence	Number of students attending online lesson for the full duration (supplemented with qualitative feedback on online delivery of lesson)	**90% or above** Continue with main trial	**70–89%** Consult research team to advise on changes to lesson delivery	**Below 70%** The main trial will need to reconsider how lesson is delivered
Fidelity of Lesson Delivery	Percentage of the lesson covered by teacher, assessed by two fidelity checkers	**90% or above** Continue with main trial	**60–89%** Consult research team on possible changes to lesson intervention or training	**Below 60%** Fully reconsider lesson intervention/training

### Study design

The main study consists of a two-arm open parallel group cluster RCT with an intervention group and a lessons-as-usual wait-list control group. Stratifying based on school size (large, medium, small), randomisation of schools will be conducted by an independent researcher blinded to conditions through block randomisation, using random block sizes of two, four, and six. Randomisation of schools will be completed following confirmation that schools recruited to the trial meet eligibility criteria, and the school principal has provided informed consent.

Cimigo and the study research team (i.e., study authors) will be informed of the study allocation, though will be blind to the size of each block during randomisation to minimise selection bias [56]. Participants will not be explicitly told their study condition, though will be made aware of the assessment time points and whether they receive the lesson between T1 and T2 (intervention) or after T3 (wait-list control). The statistician will be blinded to conditions during the trial and analysis. The trial will have assessments at baseline, post-intervention, and two-month post-intervention time points; see Fig. 1 for a flow diagram.

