### Sample size calculation

A meta-analysis of 50 RCTs evaluating single-session adolescent psychological health interventions [41] reported a mean effect size of Hedges *g* = 0.32, which can be interpreted as a small-to-medium effect size (small effect size = 0.2; medium effect size = 0.5). This is consistent with findings from the RCT evaluation of *Dove Confident Me: Single Session* [36], which reported standardised effects ranging from small to small-to-medium for outcome measures. Based on a more conservative, lower bound of d = 0.2, a sample size of *n* = 500 girls and *n* = 500 boys per arm would provide in excess of 95% power over any positive range of correlation between baseline and outcome data at T2 and would have in excess of 90% power for separate analyses for girls and boys. We will oversample to mitigate the effects of loss to follow-up due to student absence or technical difficulties to increase population coverage and external validity. Therefore, the target study sample size will be approximately 2000 adolescents: 1000 (500 girls, 500 boys) in the control condition, 1000 (500 girls, 500 boys) in the intervention condition. It is estimated that 20 eligible schools will be recruited to achieve this sample size.

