### Data analysis

Data preparation and assessment of baseline equivalence will be undertaken using SPSS 28.0 (IBM Corp, 2021). Data will be screened to ensure coding fidelity and data veracity. Data validity checks will be undertaken, and derived outcome scale data will be examined for the presence of outliers and any unduly inferential observations and to assess the distribution of scores. Analysis will proceed on an intention-to-treat basis. Analysis will be conducted with and without clusters as random effects to determine any significant impact [65]. Missing data will be assessed across outcomes and time points. A sensitivity analysis to missing data will be performed. Attention check data (greater than 70% successful completion of attention checks) will form a per-protocol analysis.

The primary analysis will be a linear mixed model with random intercepts. The model will include the three main effects, three two-way interactions, and three-way interaction for randomised arm (between-subjects fixed effect factor with two levels intervention and control), study phase (repeated measures fixed effect factor with two levels T2 and T3), gender (between-subjects fixed effects factor with two levels, male and female), including a baseline measure as a covariate, and the three two-way interactions between covariate and each of randomised arm, gender, and phase. A priori analyses will proceed primarily comparing the two randomised arms at T2 controlling for baseline covariate (a) ignoring gender (b) split by gender and (c) incorporating gender as a factor. These analyses will be repeated at T3. These prior reasoned analyses will use ANCOVA. The ANCOVA model will be extended to include a baseline by randomised arm interaction term if the homogeneity of regression lines assumption is not tenable. All models will be screened for gross deviations from underpinning assumptions to ensure valid statistical inferences are drawn.

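### School size stratifies the randomisation but is missing from the listed primary model and ANCOVAs, so the analysis does not follow the design; the cost is modest and arises only if size is prognostic after baseline adjustment

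*Protocol article*

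**What the plan says.** Under Study design, schools are the unit of randomisation and size is the only stratification factor: "Stratifying based on school size (large, medium, small), randomisation of schools will be conducted by an independent researcher". Allocation within strata is blocked, "using random block sizes of two, four, and six". Under Sample size calculation, "It is estimated that 20 eligible schools will be recruited to achieve this sample size", for about 2000 students.

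Under Data analysis, "The primary analysis will be a linear mixed model with random intercepts". The level of the intercepts is not named. The fixed effects follow as an explicit list: "The model will include the three main effects, three two-way interactions, and three-way interaction for randomised arm", study phase and gender, then "including a baseline measure as a covariate, and the three two-way interactions between covariate and each of randomised arm, gender, and phase". The supporting comparisons are specified as ANCOVA: "A priori analyses will proceed primarily comparing the two randomised arms at T2 controlling for baseline covariate", ignoring gender, split by gender, and with gender as a factor, all repeated at T3. On clustering, "Analysis will be conducted with and without clusters as random effects to determine any significant impact". School size does not appear among these terms, and no sensitivity analysis adds it.

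**The concern.** Stratifying by size roughly balances size across the arms. Whatever between-school variation size explains is therefore largely removed from the true sampling error of the arm contrast. A model without size does not know this and leaves that variation in its estimate of school variance. Where a school random effect is fitted, the standard error is then larger than it should be, and some of the precision that stratification was meant to buy is given away. With about 20 schools, between-school variation is a main limit on precision.

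The list of terms goes down to covariate-by-phase interactions. The omission is therefore a feature of the stated model, and not a detail that the article simply leaves to another document.

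**Working it through.** **Inputs from the protocol article.** 20 schools, about 2000 students allocated 1:1 (so about 100 per school), d = 0.2, and three size strata.

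**Assumptions, because the article does not give them.** Two-sided 5% level; 10 schools per arm; strata of 6, 8 and 6 schools balanced by arm; equal school sizes; ICC ρ of 0.02 to 0.05; share R² of between-school variance explained by size of 0 to 0.5; correlation r between baseline and T2; school effects stable from T1 to T2.

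**Step 1, the plan's own power figure.** With 1000 per arm and SD 1, the noncentrality is 0.2 × √(1000/2) = 4.47. This gives 99.4% power at r = 0, and more at any positive r. The stated figure (above 95%) reproduces, but as a calculation for individually randomised students. Neither schools nor strata enter it, so it says nothing about the value of the stratum.

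**Step 2, variance with and without the stratum.** Per school mean, after subtracting a student-level baseline slope r:

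- within-stratum variance: w = (1 − R²)·ρ·(1 − r)² + (1 − ρ)(1 − r²)/100
- between-stratum variance: s = R²·ρ·(1 − r)²
- true variance of the arm contrast: (4/20)·w
- variance estimated without the stratum (18 df): (4/20)·(w + (20/18)·s) on average
- inflation of the standard error: √(1 + (20/18)·s/w)

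With the stratum in the model, the residual estimates w on 16 df.

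**Step 3, two cases in full.**

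- ρ = 0.02, R² = 0.25, r = 0.5: w = 0.00375 + 0.00735 = 0.01110 and s = 0.00125. Inflation is √1.125 = 1.061. The effective critical value is 2.101 × 1.061 = 2.229 on 18 df, so the actual type I error is about 0.039.
- ρ = 0.05, R² = 0.50, r = 0.5: w = 0.00625 + 0.007125 = 0.013375 and s = 0.00625. Inflation is √1.519 = 1.233. The effective critical value is about 2.59, so the actual type I error is about 0.02.

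**Step 4, all cases.** Type I error is from the formula. Power is from simulation of school means, 40,000 runs per case.

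| r | ρ | R² | SE inflation | type I error, stratum omitted | power, omitted → included |
|---|---|---|---|---|---|
| 0.5 | 0.02 | 0.25 | 1.061 | 0.039 | 0.973 → 0.978 |
| 0.5 | 0.02 | 0.50 | 1.132 | 0.029 | 0.977 → 0.988 |
| 0.5 | 0.05 | 0.25 | 1.100 | 0.033 | 0.867 → 0.904 |
| 0.5 | 0.05 | 0.50 | 1.233 | 0.02 | 0.889 → 0.952 |
| 0.7 | 0.02 | 0.25 | 1.039 | 0.043 | 0.999 → 0.999 |
| 0.7 | 0.02 | 0.50 | 1.081 | 0.036 | above 0.999 in both |
| 0.7 | 0.05 | 0.25 | 1.073 | 0.037 | 0.994 → 0.996 |
| 0.7 | 0.05 | 0.50 | 1.163 | 0.025 | 0.996 → 0.998 |
| none | 0.02 | 0.25 | 1.106 | 0.032 | 0.69 → 0.76 |
| none | 0.02 | 0.50 | 1.249 | 0.017 | 0.707 → 0.845 |
| none | 0.05 | 0.25 | 1.138 | 0.028 | 0.39 → 0.49 |
| none | 0.05 | 0.50 | 1.344 | 0.011 | 0.36 → 0.62 |

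With the stratum included, type I error stays at about 0.05 throughout.

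**Step 5, size not prognostic (R² = 0, no baseline).** Power moves from 0.688 to 0.681 at ρ = 0.02 and from 0.415 to 0.409 at ρ = 0.05. This is the price of going from 18 to 16 df.

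**Step 6, less stable school effects.** With r = 0.7, R² = 0.25 and the remaining school effects correlated only 0.7 over time, power moves from 0.961 to 0.962 at ρ = 0.02 and from 0.768 to 0.777 at ρ = 0.05.

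**Step 7, imperfect balance.** With the random blocks of two, four and six that the article specifies, about 42% of allocations leave at least one stratum out of balance by two or more schools. Simulated with those blocks and no baseline (ρ = 0.02, R² = 0.25), type I error is 0.037 without the stratum and 0.053 with it, and power goes from 70% to 76%. The direction does not depend on perfect balance.

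**The case against.** The strongest reply is that every planned model already adjusts for the student's own baseline score. Baseline is taken about a week before the lesson and T2 about a week after it. A lasting difference between large and small schools is therefore already partly removed. This stands, and it changes the size of the point. A reader might infer losses of 7 to 26 percentage points from the rows without baseline, but those rows do not describe the planned analysis.

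Second, the article gives no ICC and nothing on whether school size predicts body esteem. A flat statement that power is lost goes further than the document allows. With no prognostic value, the stratum terms cost slightly more than they return.

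Third, a reader might infer that all the planned intervals are too wide. That holds only where a school random effect is fitted. The article does not name the level of its random intercepts and also plans analyses without clusters. There the standard errors are too small, for a separate reason. The design effect 1 + 99ρ is 1.99 at ρ = 0.01 and 5.95 at ρ = 0.05. With no baseline adjustment, a nominal 5% test then has critical values of 1.96/√1.99 = 1.39 and 1.96/√5.95 = 0.80, that is, a type I error of about 0.16 and 0.42. A stratum term does not repair that.

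Finally, a condensed article may leave covariate detail to an analysis plan. This has less force here, because the article sets out its model terms explicitly.

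**Conclusion.** The mismatch is a documented fact: the only factor that restricts the randomisation is absent from the listed mixed model and from the ANCOVAs. Its consequence is conditional and modest. Where school is a random effect and size remains prognostic after baseline adjustment, the test runs at about 0.02 to 0.045 in place of 0.05, and power is lower by about 0 to 6 points. These ranges rest on the assumed ICC, baseline correlation, share explained by size and stability of school effects; only the number of schools, the sample size and d come from the article.

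A reader might take the omission as a threat to validity. It is not one: in the clustered analysis the error is conservative, and the arm comparison stays unbiased over the randomisation. It is a matter of efficiency and of matching the analysis to the design. It is worth correcting because the possible gain exceeds the cost of under one point.

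**What to change.** Add school size, in the three categories used at randomisation, as a fixed effect in the primary mixed model and in each ANCOVA comparison at T2 and T3, with school fitted as a random effect in all of them. If the factor is to be left out, give the reason in advance. The cost is one line of text and two school-level degrees of freedom; the data are already held from the randomisation. The change should be recorded before outcome data are seen by arm, since the same adjustment made later could look data-driven. The planned analyses without cluster effects need separate attention.
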